# Equity-Centered Postdischarge Support for Medicaid-Insured People: Protocol for a Type 1 Hybrid Effectiveness-Implementation Stepped Wedge Cluster Randomized Controlled Trial

**DOI:** 10.2196/54211

**Published:** 2024-03-26

**Keywords:** health care disparities, evidence-based practice, Medicaid, transitional care, implementation science, socioeconomic disparities in health

## Abstract

**Background:**

Disparities in posthospitalization outcomes for people with chronic medical conditions and insured by Medicaid are well documented, yet interventions that mitigate them are lacking. Prevailing transitional care interventions narrowly target people aged 65 years and older, with specific disease processes, or limitedly focus on individual-level behavioral change such as self-care or symptom management, thus failing to adequately provide a holistic approach to ensure an optimal posthospital care continuum. This study evaluates the implementation of THRIVE—an evidence-based, equity-focused clinical pathway that supports Medicaid-insured individuals with multiple chronic conditions transitioning from hospital to home by focusing on the social determinants of health and systemic and structural barriers in health care delivery. THRIVE services include coordinating care, standardizing interdisciplinary communication, and addressing unmet clinical and social needs following hospital discharge.

**Objective:**

The study’s objectives are to (1) examine referral patterns, 30-day readmission, and emergency department use for participants who receive THRIVE support services compared to those receiving usual care and (2) evaluate the implementation of the THRIVE clinical pathway, including fidelity, feasibility, appropriateness, and acceptability.

**Methods:**

We will perform a sequential randomized rollout of THRIVE to case managers at the study hospital in 3 steps (4 in the first group, 4 in the second, and 5 in the third), and data collection will occur over 18 months. Inclusion criteria for THRIVE participation include (1) being Medicaid insured, dually enrolled in Medicaid and Medicare, or Medicaid eligible; (2) residing in Philadelphia; (3) having experienced a hospitalization at the study hospital for more than 24 hours with a planned discharge to home; (4) agreeing to home care at partner home care settings; and (5) being aged 18 years or older. Qualitative data will include interviews with clinicians involved in THRIVE, and quantitative data on health service use (ie, 30-day readmission, emergency department use, and primary and specialty care) will be derived from the electronic health record.

**Results:**

This project was funded in January 2023 and approved by the institutional review board on March 10, 2023. Data collection will occur from March 2023 to July 2024. Results are expected to be published in 2025.

**Conclusions:**

The THRIVE clinical pathway aims to reduce disparities and improve postdischarge care transitions for Medicaid-insured patients through a system-level intervention that is acceptable for THRIVE participants, clinicians, and their teams in hospitals and home care settings. By using our equity-focused case management services and leveraging the power of the electronic medical record, THRIVE creates efficiencies by identifying high-need patients, improving communication across acute and community-based sectors, and driving evidence-based care coordination. This study will add important findings about how the infusion of equity-focused principles in the design and evaluation of evidence-based interventions contributes to both implementation and effectiveness outcomes.

**International Registered Report Identifier (IRRID):**

DERR1-10.2196/54211

**Trial Registration:**

ClinicalTrials.gov NCT05714605; https://clinicaltrials.gov/ct2/show/NCT05714605

## Introduction

### Background

Complex care management provides critical support in the days and weeks following hospitalization for individuals with multiple chronic conditions. This postdischarge support can be especially beneficial for nearly 80 million individuals in the United States who are insured by Medicaid [1] and experience higher rates of chronic illness [2], more frequent hospitalizations, and worse clinical outcomes following discharge [3-5]. Readmissions among adults insured by Medicaid ages 45-64 years stand at 24% compared to 20% for older adults insured by Medicare [6]. Similarly, about 34% of individuals insured by Medicaid will experience an emergency department (ED) visit annually, far exceeding the rates of those insured commercially [7]. They experience deficits in primary care assessment and treatment and fewer preventive treatments and guideline-concordant care [8,9]. Thus, Medicaid-insured patients may present to the hospital with poorly managed chronic medical conditions compared with other patients and subsequently require more intensive transitional care coordination in the aftermath of a hospitalization. The need to improve support for Medicaid-insured people following hospitalization prompted our development of the THRIVE clinical pathway. THRIVE is a clinical pathway that supports Medicaid-insured individuals with multiple chronic conditions transitioning from hospital to home by coordinating care, standardizing communication, and addressing unmet needs following hospital discharge, including the social determinants of health.

Most existing postdischarge or transitional care programs were not developed to attend to the specific needs of people insured by Medicaid and instead support older adults or patients with specific chronic illnesses such as heart failure. Other postdischarge support programs require the addition of trained health care providers such as advanced practice nurses or patient navigators to coordinate care [10-12]. At least 1 randomized controlled trial (RCT) evaluating the use of community health workers (CHWs) has demonstrated lower rates of rehospitalization for enrolled low-income individuals with significant social needs [13]. Despite facilitating important links to community-based services, CHWs are unable to manage clinical needs [13-15]. Other postdischarge support programs such as the Camden Coalition Care Model provide transitional care support to people with significant social needs with high rates of health care use, many of whom are insured through Medicaid [16]. An RCT of the Camden Coalition Care Model demonstrated no differences in readmissions at 180 days between treatment and comparison [17]. The care transitions innovation model also provides transitional care support for economically disadvantaged adults, although an RCT found no reductions in 30-day readmissions or ED use [12]. At least 3 additional studies by Liss et al [18], Balaban et al [19], and Jackson et al [20] featured weekly health coaching, self-management education, and medical home follow-up for medically and socially complex patients, although the results of these interventions have been mixed. Inconsistent findings among existing postdischarge support programs suggest the need for alternative innovations that focus on systemic and structural barriers in health care delivery.

Similar to other inequities, posthospitalization disparities among people insured by Medicaid can be traced to a long history of institutional and economic inequities impacting care delivery and outcomes. Racial and ethnically minoritized populations are overrepresented in Medicaid compared to other forms of insurance, with approximately half of Medicaid enrollees younger than 65 years of age being members of racial and ethnically diverse backgrounds [21]. With incomes 138% below the federal poverty level [22], people insured by Medicaid experience the impact of the social determinants of health, including higher levels of financial strain and concerns over out-of-pocket costs, and experience more challenges in accessing specialists and community-based care [23-28]. People insured by Medicaid are also more likely to experience the impact of systemic and institutional racism. Systemic racism refers to the distribution of goods and services in such a way that advantages one group over another or fails to provide adequate resources in the face of need. Systemic factors such as inadequate discharge planning and poor care coordination similarly contribute to unfavorable posthospitalization outcomes [21,27-29]. Interpersonal racism is often expressed through bias and discrimination and is often expressed through microaggressions and stigmatizing language. Distinct from Medicare, Medicaid has its roots in the public welfare system, which has resulted in significant social stigma. Medicaid beneficiaries have described encounters with medical professionals where they were subjected to racial and socioeconomic prejudice [29,30]. These experiences may result in the avoidance of health care settings altogether and more difficulties accessing timely specialty care, all of which paradoxically increase ED use or lead to avoidable hospitalizations due to delayed management of chronic illnesses [31,32].

Given the long-standing disparities experienced by people insured by Medicaid during and following hospitalization, there is a need for transitional care support focused on systemic and structural barriers to care and social determinants of health. The Centers for Disease Control and Prevention [33] defines health equity as “the state where everyone has a fair and just opportunity to attain their highest level of health.” Using an equity lens draws attention to those at greatest risk to how social and economic strata shape access to material resources while also identifying the impact of marginalizing conditions such as racism and health resource constraints that intersect and result in disparate outcomes [34]. Using an equity lens also emphasizes what Peterson et al [35] refer to as the multiple, intersecting spheres of power, defined as the practices, processes, and policies that determine the distribution and access to resources and opportunities needed to be healthy. These spheres of power intersect with individual factors (eg, personal agency) to produce disparate outcomes. From this perspective, addressing postdischarge disparities requires a focus on optimizing service delivery and interdisciplinary collaborations across settings.

### Codeveloping the THRIVE Clinical Pathway

Using an equity lens, our interdisciplinary team of clinicians, researchers, and community members formed to engage in meaningful action to support people insured by Medicaid and transform health care practices and processes that impeded sufficient transitional care support [36]. We began with months of participatory activities informed by an equity lens and principles of human-centered design [37], machine learning [38], and mixed methods approaches [39], which culminated in the development of THRIVE [40]. The THRIVE clinical pathway was launched in a large Level 1 Trauma Center in Philadelphia in 2019 and includes five core components: (1) the identification of individuals insured by Medicaid and coordination of home care referral during discharge planning while hospitalized; (2) provision of immediate home care services where nurses perform medication reconciliation, intensive teaching, and chronic disease management; (3) continued clinical oversight by discharging physicians; and (4) standardized communication between community and acute care providers via web-based case management that (5) prioritizes health-related social needs such as housing or food insecurity faced by Medicaid-insured patients (Figure 1). Our work as a team is anchored by our advisory board, which is comprised of community members, some of whom are Medicaid insured. The THRIVE Community Advisory Board meets quarterly to meaningfully engage past THRIVE participants, caregivers, and community members to ensure that the program goals are rooted in the vision and values of the community we serve.

In many health care settings, posthospitalization disparities among economically disadvantaged people are linked to personal deficits or behaviors. They are often referred to by their volume of health resource use, invariably referred to as “high-cost high needs,” “superusers,” “frequent flyers,” “noncompliant,” or “bounce backs,” and are essentially blamed for poor outcomes. From this perspective, postdischarge disparities are often regarded as immutable social circumstances or moral failures beyond the purview of medicine’s reach instead of a result of the impact of the social determinants of health, structural determinants such as failures in service delivery (eg, fragmented care coordination), and interpersonal racism [41]. In developing THRIVE, we sought to counter long-standing stigmatizing views and instead directed our focus on re-engineering service delivery and intensifying resources to those most in need while maintaining active involvement with affected community members in programmatic design and sustainability efforts.

Published results from a nonrandomized pilot of the first year of the THRIVE pathway revealed that participants experienced increased connections to postacute care services, including social support, and a 50% decrease in rates of 30-day readmissions and ED use compared to patients receiving standard care [42]. With these early findings, we are now poised to evaluate a scalable and sustainable postdischarge management process in a new setting and with a more rigorous evaluation and attention to organizational factors influencing success.

This study will deploy a type 1 hybrid effectiveness-implementation stepped wedge cluster RCT across a single hospital in Philadelphia [43]. The advantage of this trial design is that it offers an efficient and practical way to introduce THRIVE to new sites while reducing the ethical concerns of withholding an intervention that has shown benefit for economically disadvantaged populations. This study will also be guided by the Exploration, Preparation, Implementation, Sustainment framework; Proctor’s outcomes framework; and the Health Equity Implementation Framework (HEIF) [44-46]. The HEIF adapts the Integrated Promoting Action on Research in Implementation in Health Services framework. The HEIF proposes determinants that are believed to predict the successful and equitable implementation of an intervention. The 3 health equity domains included in the HEIF include cultural factors, clinical encounter factors, and societal context [47]. Our use of the framework will help us to detect any factors that might lead to uneven referrals to THRIVE; disparate benefits to the intervention; and any barriers that might prevent organizations, health care providers, or administrators from engaging in the intervention. In their recently published paper, Brownson et al [48] noted that “Incorporating a strong equity focus in implementation science requires not only a deliberate emphasis on the needs, culture, and history of the populations and communities but also more critical analyses and deeper understanding of systems and policies, including care delivery and provider attitudes from which inequities might arise.” They propose action steps for making health equity more prominent in implementation science. To that end, we incorporate and adapt our study design to ensure principles of equity in the approach to data collection, measures, contextual alignment, and dissemination practices (Table 1).

**Figure 1 figure1:**
[figure not shown]
Components of the THRIVE clinical pathway. APP: advanced practice provider; EHR: electronic health record; MD: medical doctor; OT: occupational therapy; PRN: pro re nata (as needed); PT: physical therapy; RN: registered nurse; SW: social worker.

**Table 1 table1:** Equity-relevant domains included in the implementation and outcome evaluation of THRIVE [48].

Domain	Recommendation	Core elements within this study
Evidence base	Link social determinants with health outcomes	Implement THRIVE for all Medicaid-insured individuals at a new study site to meet the postdischarge clinical and social needs of an economically disadvantaged population.
Methods and measures	Integrate equity into implementation models	Incorporate the 3 domains of the Health Equity Implementation Framework into the implementation evaluation.
Context	Engage organizations in internal and external equity efforts	Engage with clinical partners, administrators, and community advisory board members to implement THRIVE at a new site.
Cross-cutting issues	Focus on equity in dissemination efforts	Plan activities with THRIVE Community Advisory Board to disseminate study results.

### Aims and Hypotheses

The specific aims of this research are to:

Examine referral patterns, 30-day readmission, and ED use patterns for participants who receive THRIVE support services compared to those receiving usual care.Hypothesis 1: We anticipate that referral patterns will increase and that 30-day readmissions and ED use will decrease for THRIVE participants compared to usual care.Evaluate the implementation of the THRIVE clinical pathway, including fidelity, feasibility, appropriateness, and acceptability.

## Methods

### Overview

Our study methods are described per the SPIRIT (Standard Protocol Items: Recommendations for Interventional Trials) statement and the CONSORT (Consolidated Standards of Reporting Trials) extension for stepped wedge cluster RCTs [49,50]. The SPIRIT and CONSORT checklists are included as Multimedia Appendices 1 and 2.

### Study Setting

The study setting includes a single site—Pennsylvania Hospital (PAH), the nation’s first acute care setting in the country and 1 of 6 hospitals in the University of Pennsylvania Health System. More than 50% of PAH’s patient population on the hospitalist service self-identify as racial or ethnic minority individuals, and >25% are Medicaid insured [34]. PAH provides over 40,000 ED visits and >18,000 adult admissions annually.

### Design and Randomization

#### Overview

This is a prospective single-site type 1 hybrid effectiveness-implementation pragmatic stepped wedge cluster RCT. Our stepped wedge design will include a sequential randomized rollout of the intervention to case managers at PAH in 3 steps, and data collection will occur over 18 months. This mixed methods (quantitative and qualitative) study design involves simultaneous collection and analysis of quantitative and qualitative data, giving priority weight to the quantitative data to evaluate program referrals, outcomes, and program fidelity, while qualitative data will evaluate the process through detailed descriptions of perspectives of barriers and facilitators faced by health care providers in implementing the THRIVE intervention [51]. This study includes qualitative interviews and surveys of clinicians and administrators to assess their perspectives on appropriateness, feasibility, and acceptability of THRIVE. Nesting the qualitative interviews within an RCT of the THRIVE intervention will allow us to determine whether the intervention improved primary outcomes (referrals to home care, 30-day readmission, ED use, and connection to primary care providers) and to identify professional and organizational barriers to implementation. Combining these insights with effectiveness outcome data will allow consideration for meaningful contextual factors that are considered critical to the implementation of THRIVE and subsequent outcomes.

#### Randomization

Groups of case managers (4 in the first group, 4 in the second, and 5 in the third) were randomly assigned by the study methodologist to each sequence using a random number generator. A stepped wedge design—that is, a 1-time crossover design—was used for THRIVE (Table 2).

Specifically, following a baseline data collection period, 4 case managers will be randomized to receive training on the THRIVE clinical pathway. Following training, they begin referring to the THRIVE clinical pathway. At 8-week intervals, the remaining case managers will be trained in the THRIVE intervention and will be able to begin submitting referrals. Since case managers from the sequences work within the same space, the ability to conceal allocation was limited; however, all case managers were made aware of their upcoming ability to refer to the THRIVE clinical pathway.

**Table 2 table2:** Study design for the type 1 hybrid effectiveness-implementation stepped wedge cluster randomized controlled trial of the THRIVE clinical pathway.

Cluster	Baseline (3 months)	Enrollment period 1 (8 weeks)	Enrollment period 2 (8 weeks)	Enrollment period 3 (8 weeks)	Follow-up (18 months)
Sequence 1 (4 case managers)		✓	✓	✓	✓
Sequence 2 (4 case managers)			✓	✓	✓
Sequence 3 (5 case managers)				✓	✓

### THRIVE Eligibility Criteria

Individuals eligible for a THRIVE referral include (1) being Medicaid insured, dually enrolled in Medicaid and Medicare, or Medicaid eligible; (2) residing in Philadelphia; (3) having experienced a hospitalization at the study hospital for more than 24 hours with a planned discharge to home; (4) agreeing to home care at partner home care settings; and (5) being aged 18 years or older. If home care services are declined at any time following discharge, THRIVE services are also discontinued. If palliative or hospice services are ordered following discharge, THRIVE services will not be offered.

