### The THRIVE Intervention

#### Current Usual Care

To provide evidence of the effectiveness and implementation of THRIVE, we will compare individuals receiving THRIVE services to patients receiving usual care. The current usual care will serve as the control condition that patients will receive during the control phases of the design. Usual care may include discharge care planning that reflects the patient’s medical needs, which may or may not include referrals to home care, skilled nursing or rehabilitation facilities, and other outpatient services.

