##### Outcomes and Measures

The primary outcome includes the referral rate to home care made by CMs compared to baseline and the nonrandomized cluster. The secondary outcomes are 30-day readmissions and ED visits. Additional covariate data at the patient (eg, demographics and comorbidities) and unit levels (eg, type of unit and discharging team or provider) will be collected from analyses. For THRIVE participants, these outcomes will be assessed from the date of hospitalization, which resulted in a referral to THRIVE. For the usual care group, we will identify all readmissions and ED visits occurring after the first index hospitalization identified in the EHR for the calendar year of the study. Outcome measures, guiding framework, data sources, collection, and timing are described in Table 3.

**Table 3 table3:** Summary of outcomes, measures, data sources, collection method, and timing.

Construct and framework					Design		Method of collection			Timing	
**Aim 1: Examine referral patterns, 30-day readmission, and ED^a^ use patterns for participants who receive THRIVE support services compared to those receiving usual care**											
	THRIVE referrals^b^ 30-day readmissions^c^ 30-day ED visits^c^ Primary care visit within 30 days of discharge^c^ Specialty care visit within 30 days of discharge^c^			Stepped wedge cluster randomized controlled trial		Electronic health record			Baseline and at the study end		
**Aim 2: Evaluate the implementation of the THRIVE clinical pathway, including fidelity, feasibility, appropriateness, and acceptability**											

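### The planned-home-discharge restriction binds THRIVE participants but is not stated for the usual-care comparator, so the 30-day contrasts can differ by discharge destination without any THRIVE effect

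*Protocol article*

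**What the plan says.** **Who can be a THRIVE participant.** The third criterion under THRIVE Eligibility Criteria is "having experienced a hospitalization at the study hospital for more than 24 hours with a planned discharge to home". The fourth is "agreeing to home care at partner home care settings".

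**What the control condition is.** Under Current Usual Care: "The current usual care will serve as the control condition that patients will receive during the control phases of the design". That care consists of discharge planning, "which may or may not include referrals to home care, skilled nursing or rehabilitation facilities, and other outpatient services".

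**How usual-care outcomes are found.** Under Aim 1, Outcomes and Measures, for the usual care group "we will identify all readmissions and ED visits occurring after the first index hospitalization identified in the EHR". The sentence gives a calendar-year window but no condition on destination.

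**What is compared.** Table 3, footnote c, sets THRIVE participants against the usual care group for 30-day readmission, ED visits, primary care visits and specialty visits. It puts no eligibility limit on the comparator.

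**Referral.** Outcomes and Measures says: "The primary outcome includes the referral rate to home care made by CMs compared to baseline and the nonrandomized cluster". No denominator is given there. Table 3, footnote b, defines the referral measure as the proportion of THRIVE-eligible patients who are referred to THRIVE.

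**Adjustment.** The covariate examples are demographics, comorbidities, unit type and discharging team or provider. The Analysis section adds random effects for the medical team and fixed effects for time. Discharge destination appears in neither place.

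**The concern.** One side of each 30-day contrast is filtered on destination and the other, as written, is not. A patient sent to a nursing or rehabilitation facility can be a usual-care index stay but cannot be a THRIVE participant. Such patients may differ in their risk of readmission, and it is plausible, though the article does not say so, that they make fewer ordinary primary care visits in the following 30 days. Their presence on one side only would then produce a difference that has nothing to do with THRIVE.

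Randomising case managers does not remove this if the third criterion screens stays only in the THRIVE condition. Team effects and time effects do not correct for who is admitted to each condition. At stake is whether a difference in readmission, ED use or connection to outpatient care can be read as an effect of the pathway.

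**Working it through.** **The plan's own figures.** The Sample Size section gives 236 per group for readmissions and 267 per group for ED visits (80% power, .05 level) without the event rates behind them, so neither can be reproduced or faulted. The article's background readmission rate of 24%, halved as in the pilot, gives 160 per group (pooled two-proportion formula, two-sided). With a halving, 236 per group corresponds to about 17.3% against 8.7%, and 267 per group to a control rate of about 15.5%. This point disputes no sample size; 236 and 267 serve below only as group sizes.

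**Inputs for the shift.**
- s, the share of usual-care index stays discharged to a facility: not in the article; 10%, 20% and 30% assumed.
- Readmission among home discharges: 24%, borrowed from the Background figure for Medicaid adults aged 45–64. Facility rate: 15%, 24% or 35%, assumed.
- Primary care visit within 30 days: 50% after home discharge and 25% or 10% after facility discharge, all assumed.
- Home care referral: 20%, 30% or 50% among home discharges and 0% among facility discharges, all assumed.

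**Formulas, with no THRIVE effect.** The THRIVE side has the home rate p_H. The usual-care side has p_U = (1 − s)·p_H + s·p_F, where p_F is the facility rate. The spurious shift is d = p_U − p_H = s·(p_F − p_H). The chance of a nominally significant result is Φ(−1.96 + d/SE) + Φ(−1.96 − d/SE), with SE² = p_H(1 − p_H)/n + p_U(1 − p_U)/n. This is a simple two-group test on independent patients, not the planned mixed model, so the probabilities are indicative only.

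**Worked cases.**
- Readmission, s = 30%, p_F = 35%: d = 0.30 × 0.11 = 0.033; SE = 0.0402 at n = 236; probability 13.0%.
- Primary care, s = 30%, p_F = 10%: d = 0.30 × (−0.40) = −0.12; SE = 0.0426 at n = 267; probability 80.3%.

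**Usual-care rate, with the chance of a false significant result in brackets.**

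| Outcome (home rate, facility rate) | s = 10% | s = 20% | s = 30% |
|---|---|---|---|
| Readmission (24%, 15%), n = 236 | 23.1% (5.6%) | 22.2% (7.5%) | 21.3% (10.8%) |
| Readmission (24%, 24%), n = 236 | 24.0% (5.0%) | 24.0% (5.0%) | 24.0% (5.0%) |
| Readmission (24%, 35%), n = 236 | 25.1% (5.9%) | 26.2% (8.5%) | 27.3% (13.0%) |
| Primary care visit (50%, 25%), n = 267 | 47.5% (8.9%) | 45.0% (21.2%) | 42.5% (41.4%) |
| Primary care visit (50%, 10%), n = 267 | 46.0% (15.2%) | 42.0% (46.0%) | 38.0% (80.3%) |

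The readmission shift runs from −2.7 to +3.3 points and is zero when facility and home rates agree. The primary care shift is 2.5 to 12 points. The same formula applies to ED and specialty visits, but the article offers nothing to anchor a facility rate for either.

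**Referral, only if all discharges are the denominator.** Home rates of 20%, 30% and 50% fall to 18%, 27% and 45% at s = 10%, and to 14%, 21% and 35% at s = 30%. That is a shift of 2–5 points (probability 9–21%) rising to 6–15 points (46–94%). With footnote b's denominator, s = 0 and the shift vanishes. But footnote b counts THRIVE referrals, which case managers begin to make only after training (Randomization). It therefore cannot supply the baseline comparison of home care referral that Outcomes and Measures promises.

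**With a common restriction.** s = 0 gives d = 0 and a rejection probability of 5%.

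**The case against.** The strongest reply is that a condensed article has been read too literally. The sentence on usual-care events says which events count after the index stay. It states no insurance, residence, age or length-of-stay limit either, so taken as a full cohort definition it would admit patients nobody intends to include. All-payer data are reserved for a secondary analysis, which suggests that the main comparator is restricted, and the referral dashboard already tracks eligible patients who were not referred. The cohort detail may sit in the full protocol. This reply narrows the point but does not remove it. The article states a rule for the comparator, allows facility referral in its description of usual care, and names no adjustment for destination.

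Four stronger readings are tempting and are not supported:
- A reader might infer that the usual-care group is defined to include facility patients. The Current Usual Care text describes the content of care; it permits such patients and nowhere excludes them.
- A reader might infer that the referral outcome is biased. Footnote b restricts its denominator to eligible patients, so this depends on which of the two definitions governs.
- A reader might infer that every shift favours THRIVE. For readmission the sign depends on an unknown facility rate.
- A reader might add in-hospital deaths, transfers and departures against advice to the comparator. The article mentions none of these, and footnote c counts outcomes from discharge, which fits poorly with including deaths.

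It is also fair to object that filtering on actual disposition is not the same as filtering on planned discharge, and that THRIVE acts in the very step where destination is decided. That stands, and it shapes the remedy.

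**Conclusion.** The point holds in limited form. As written, the home-discharge restriction applies to THRIVE participants and is not stated for the usual-care group, so the readmission, ED, primary care and specialty care contrasts can reflect destination rather than THRIVE. The article does not allow the size to be determined. On the assumed shares and rates, the readmission shift is at most about three points in either direction and adds little to the false-positive rate (up to 13%). The primary care shift could be considerably larger, but it rests wholly on assumed visit rates. For referral the matter is an inconsistency between two definitions, to be reconciled, rather than an established bias. The change should be made; it does not affect the stated sample size. Confidence is medium, because an unseen full protocol may already apply the restriction.

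**What to change.** 1. In Current Usual Care and in Outcomes and Measures, state that index stays in both control and THRIVE conditions must meet the same observable eligibility criteria: insurance, residence, age, stay of more than 24 hours, and planned home discharge. Where the plan is not recorded, use the EHR disposition field as a proxy and say so.
2. Use that one set of stays as the denominator for the referral rate in every period, and bring Outcomes and Measures and Table 3 footnote b into line on which referral is counted and among whom.
3. Report the share of otherwise eligible stays discharged home, by condition and period.
4. Repeat Aim 1 without the destination filter in both conditions as a sensitivity analysis, because trained case managers may change where patients go and the filter could then itself alter who is compared.

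Agreement to home care is a separate mismatch that this filter does not resolve.

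The cost is one EHR filter, a few sentences, one descriptive table and one further model run. The downside is fewer comparator records and possibly a less favourable contrast.
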